## Abstract

**Background:**

Neurotoxicity caused by treatment for a brain tumor is a major cause of neurocognitive decline in survivors. Studies have shown that neurofeedback may enhance neurocognitive functioning. This paper describes the protocol of the PRISMA study, a randomized controlled trial to investigate the efficacy of neurofeedback to improve neurocognitive functioning in children treated for a brain tumor.

**Methods/Design:**

Efficacy of neurofeedback will be compared to placebo training in a randomized controlled double-blind trial. A total of 70 brain tumor survivors in the age range of 8 to 18 years will be recruited. Inclusion also requires caregiver-reported neurocognitive problems and being off treatment for more than two years. A group of 35 healthy siblings will be included as the control group. On the basis of a qEEG patients will be assigned to one of three treatment protocols. Thereafter patients will be randomized to receive either neurofeedback training (n=35) or placebo training (n=35). Neurocognitive tests, and questionnaires administered to the patient, caregivers, and teacher, will be used to evaluate pre- and post-intervention functioning, as well as at 6-month follow-up. Siblings will be administered the same tests and questionnaires once.

**Discussion:**

If neurofeedback proves to be effective for pediatric brain tumor survivors, this can be a valuable addition to the scarce interventions available to improve neurocognitive and psychosocial functioning.

**Trial registration:**

ClinicalTrials.gov NCT00961922.

## Background

As a result of improved treatment, the survival rate of children diagnosed with a brain tumor has increased considerably [1]. As a consequence, neurocognitive long-term effects of the tumor and the treatment are reported more often, including deficits in attention, processing speed, and memory [2-4]. Radiotherapy, chemotherapy, tumor location, and longer time since diagnosis are related to worse neurocognitive functioning [5,6]. A major consequence of these impairments is the decline in ability to acquire new skills and information, which leads to an increasing gap in the development between patients and their peers. This, in turn, has its impact on educational results, vocational success and may compromise social competence and quality of life [7].

Butler and Mulhern have emphasized that interventions should be developed to improve neurocognitive functioning and subsequently improve future perspectives of these children [8]. Interventions that are considered relevant for survivors with cancer-related brain injury are cognitive remediation and pharmacotherapy [9,10]. A cognitive remediation program, using techniques from three disciplines: brain injury rehabilitation, special education and clinical psychology, has been developed and tested by Butler and colleagues [9]. Participants in the randomized controlled trial were 161 survivors of a childhood cancer, whose malignancy and/or treatment involved the central nervous system. The results showed improvements in caregiver reported attention and academic achievement, although the effect sizes were modest. Van ‘t Hooft et al. have investigated the effects of a cognitive training program on neurocognitive function with a randomized controlled trial, enrolling 38 patients with acquired brain injury, including 14 brain tumor survivors [10]. The training program consisted of memory and attention exercises, in combination with cognitive behavioral training. The children in the treatment group showed sustained positive effects on memory and attention functioning until six months after the training, but not on processing speed.

Regarding pharmacotherapy, it has been suggested that survivors of childhood cancer may benefit from stimulant medication as used in the treatment of attention deficit hyperactivity disorder (ADHD). Attention deficits in survivors of brain tumors are likely to improve by methylphenidate. Mulhern and colleagues found improvements of attention in 37 long term survivors of a malignant brain tumor after methylphenidate [11]. In a randomized placebo-controlled double-blinded trial including 32 survivors of a brain tumor (n=25) or acute lymphoblastic leukemia (n=7), Thompson et al. found that methylphenidate led to improved sustained attention [12]. A drawback of pharmacotherapy is the possibility of side effects, e.g. sleep disturbance, weight loss, anxiety, and sadness [13]. Also, this medication does not lead to a sustained effect unless the patient continues the pharmacotherapy.

The limited current available options warrant the search for alternatives. Neurofeedback is a relatively new form of therapy, which has never been investigated in pediatric brain tumor survivors. Neurofeedback is a behavioral intervention that is based on the principles of operant conditioning. During the therapy the patient is presented with real-time feedback on his or her brainwaves, as measured by one or more electrodes on the scalp. The patient is reinforced when the brain produces a certain desired wave. Reinforcement may comprise seeing a movie or hearing music. The desired brain wave is determined by a quantified electro encephalogram (qEEG), which is conducted prior to the training.

The effects of neurofeedback have been discovered serendipitously by Sterman, when cats having received feedback of 12–15 Hz on the motor cortex showed to be less susceptible to epileptic seizures [14]. There is a large body of scientific research documenting the effectiveness of neurofeedback for the treatment of diverse pathological conditions as summarized in comprehensive reviews, including ADHD, traumatic brain injury and schizophrenia [15-19].

Strehl et al. showed that children with ADHD were able to learn to regulate their brain activity by neurofeedback [20]. After training, significant improvements in behavior, attention, and IQ scores were found. All changes proved to be stable at six months follow-up after the end of training. Hodgson et al. conclude in their meta-analysis on nonpharmacological interventions for ADHD that neurofeedback resulted in significant improvements of DSM-IV symptoms of ADHD, neurocognitive functioning and behavior [18]. In a comparative study researchers found that the positive effects of neurofeedback for children with ADHD were superior to a computerized attention training at six months follow up [21]. However, to date there is a lack of published studies that employ a randomized placebo-controlled double-blind design when investigating neurofeedback [22].

Brain tumor survivors differ from ADHD patients, as they have structural brain damage caused by the tumor, surgery, radiotherapy and/or chemotherapy. An indication that neurofeedback might be effective in pediatric brain tumor survivors may be derived from the results of studies into the effects of neurofeedback in patients with traumatic brain injury. A review of Thornton and colleagues [23] describes a total of 44 studies (12 RCT, 16 comparative, 16 correlation) with traumatic brain injury patients reporting improved attention, cognitive flexibility, cognitive performance, and problem solving after neurofeedback, providing strong initial support for the idea that neurofeedback could be used in patients with structural brain damage. Subsequently, Aukema and colleagues conducted a pilot study into the feasibility of neurofeedback on 9 brain tumor survivors in our hospital [24]. This study demonstrated that it was feasible to use neurofeedback with brain tumor survivors. All participants completed the training and were positive about the training they received, as they would recommend it to others. Patients reported decreased subjective fatigue after the training. Also the test results showed that processing speed improved in 6 out of 9 patients. These findings warranted the set up of a larger study into the effectiveness of neurofeedback for pediatric brain tumor survivors.

The current paper describes the protocol of the PRISMA study (pediatric research on improving speed, memory, and attention); a randomized controlled double-blind trial, approved by the medical ethical committee of the Academic Medical Centre in Amsterdam. The primary aim of the PRISMA study is to investigate the efficacy of neurofeedback for improving neurocognitive functioning after treatment for a pediatric brain tumor. Secondary, we hypothesize that subsequent to the expected neurocognitive changes achieved with neurofeedback, children will experience improved psychosocial functioning [25]. Neurocognitive functioning will be investigated by tests administered to the patient. Psychosocial functioning will be measured using patient-reported as well as caregiver and teacher reported questionnaires. Assessments will take place pre and post training, as well as six months post training, in order to examine the long-term effects of the training. Comparing the effects of neurofeedback to placebo feedback will assess efficacy of neurofeedback. Pre training results obtained with the brain tumor survivors will be compared to a control group of healthy siblings, to assess the level of dysfunction on the measures used in this study.

## Methods

### Study design

This study is a randomized placebo-controlled double-blind trial, to investigate whether neurofeedback improves neurocognitive functioning in children who have received treatment for a brain tumor (trial number clinicaltrials.gov NCT00961922). After enrollment, patients will be randomized into two groups: (1a) the experimental group, receiving neurofeedback, and (1b) the placebo group, receiving placebo training. In addition, (2) a control group of healthy siblings is included; this group will not receive any training. If effectiveness of neurofeedback is demonstrated after completion of the study, patients in the placebo group will be given the opportunity to receive neurofeedback.

### Participants

Eligible for inclusion are patients in the Netherlands, aged 8 to 18 years, who finished treatment for a brain tumor at least two years prior to enrolment and who suffer from problems in neurocognitive functioning. Problems in neurocognitive functioning include attention problems, problems with information processing speed and/or memory problems as assessed by caregiver report. Exclusion criteria are premorbid diagnosis of ADHD or ADD, a mental or physical condition that prohibits neurocognitive assessment and insufficient mastery of the Dutch language. Siblings, aged between 8 and 18 years, form the control group.

### Intervention

The neurofeedback training is performed at home or school using a Dell notebook (Inspiron N5030, 15.6 inch screen), with BioExplorer software, version 1.5 installed, and a portable Brainquiry PET neurofeedback device [26,27]. Reinforcement is provided by a self-selected movie that will be presented on the screen if the brain produces the desired activity, as detected by an electrode placed at Cz (see Figure 1). Each patient receives two sessions weekly for 15 weeks, 30 sessions in total. Each session takes 39 minutes to administer, divided in ten blocks of three-minutes training, alternated with one-minute breaks. In the breaks the patient will be instructed to sit quietly with the eyes closed.

**Figure 1 F1:**
[figure not shown]
**EEG locations. Patients in PRISMA are trained on location Cz.** Location Cz is the location exactly halfway between the nasion (the bridge of the nose) and the inion (the most prominent point on the lower rear of the skull) and halfway between the two ears.

The neurofeedback sessions are hosted by extensively trained research assistants who have successfully completed a full day schooling session on administration of the neurofeedback training in accordance with detailed standard operating procedures. During the first neurofeedback session, the research assistant will be accompanied by one of the researchers to ensure adherence to the standard operating procedures. After each session, the research assistant is required to fill out a checklist providing information about the training that includes items on start and finish time of the training, duration of the session, selected movie, alertness of the patient, and any deviations from the standard procedures. Checklists are e-mailed to the researchers on a weekly basis.

#### Neurofeedback treatment modules

The neurofeedback treatment modules were developed in the software program BioExplorer. To increase comparability, we decided to develop three standard treatment modules based on the qEEGs from the pilot study [24], rather than designing an individualized treatment module for each participant. The three treatment modules are (1) beta 1 up training, (2) sensory motor rhythm (SMR) up/beta 1 down training, and (3) beta 1 down training. The qEEG of the patient determines the most suitable of the three neurofeedback treatment modules. The mean Z-score for the power in the beta 1 frequency band (15–20 Hz) for the electrodes on locations Fcz, Cz, C3, C4 and Cpz are calculated (see Figure 1). For SMR no Z-scores are provided in the brain resource report. SMR power is calculated and p-values are obtained over the average of 9 electrodes (F3, Fz, F4, C3, Cz, C4, P3, Pz and P4). The *beta 1 up training* is given if the beta 1 power is within the normal range (within 1 standard deviation from the mean) or lowered (more than 1 standard deviation below the mean). The *SMR up/beta 1 down training* is chosen if the beta 1 power is elevated (more than 1 standard deviation above the mean) and SMR (12–15 Hz) is within the normal range (p>0.05) or lowered (p<0.05). The *beta 1 down training* is chosen if the patient has beta spindles, ascertained by an EEG specialist via observation, or if both beta 1 is elevated (more than 1 standard deviation above the mean) and SMR power is elevated (p<0.05). Three identical placebo treatment modules were matched to the three neurofeedback treatment modules; beta 1 up placebo, SMR up/beta 1 down placebo and beta 1 down placebo. In the placebo treatment modules, the provided reward of a movie is not based on the desired brain waves from the patient, but on the ‘random signal generator’ that is incorporated in the BioExplorer software.

All treatment modules are set at an automatic threshold of 80% reward. This means that the threshold of reward is regularly adjusted in a way that the child sees the movie approximately 80% of the time and 20% of the time the screen of the laptop briefly turns black. Elevated muscular tension and electrical noise from surrounding devices (e.g. a lamp) can decrease the quality of the training; therefore we employ a threshold of 10 μV for muscular tension (> 55 Hz) and 50 μV for noise (range 48–52 Hz). If the muscular tension and/or the noise reach above the threshold, the movie is interrupted and the computer makes a beeping sound. The training will not continue until the muscular tension and/or noise are brought back under the threshold. This applies to the neurofeedback treatment modules as well as the placebo treatment modules.

### Randomization

The three neurofeedback treatment modules and three placebo treatment modules have been designed to have the exact same appearance on the screen of the notebook, in order to be indistinguishable during training. The six treatment modules have randomly been assigned a number (treatment module 1–6). [name], one of the members of the research team, holds the key to the codes; the other members are blinded. Another member of the research team analyzes the qEEG and informs [name] which of the three neurofeedback treatment modules is indicated according to the protocol (see Figure 2). [name] is then responsible for randomizing the patient into the actual neurofeedback or the placebo training using a randomization table generated by SPSS. For stratfication purposes, randomization takes place after selection of the most appropriate neurofeedback treatment module. After randomization, [name] notifies [name] of the assigned treatment module (treatment module 1–6) and [name] sends the assigned treatment module via email to the designated research assistant providing the neurofeedback training. Due to his not-blind status, [name] is not involved in training any patients or the processing of the data.

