### Power calculation

Power calculations used the neurocognitive measures as primary outcome measures. The calculations were done in the statistical program nQuery Advisor [45]. We expect that the neurofeedback will have a medium (d=0.5) to large effect (d=0.8) on neurocognitive functioning as measured at T1 and compared to T0, based on improvements found in children with ADHD who were trained with neurofeedback and on the improvements found in learning-impaired childhood cancer survivors treated with methylphenidate [12,15]. Given an effect size of 0.6 with alpha set at 0.05 (one-sided) and a power of 0.80, a minimum of 35 patients is required in both the neurofeedback group and the placebo group.

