### Statistical analyses

Intention-to-treat analyses will be conducted. Because of possible withdrawal before treatment starts, dropouts during the study, failure to fill out questionnaires, or research procedure violations, missing data will occur. Imputation of missing values will be carried out as much as possible to make intention-to-treat analyses feasible. Missing data will be imputed using Imputation and Variance Estimation Software [46].

Prior to the training (T0) we will assess differences between patients and siblings on neurocognitive and psychosocial functioning, using mixed modelling. Subsequently, we will conduct multivariate analysis of variance (MANOVA) to determine the effect of neurofeedback post-treatment (T1) on the primary and secondary outcomes, comparing the patients in the neurofeedback group to the patients in the placebo group. To control for possible differences in neurocognitive functioning prior to the training, T0 data will be included in the model as covariate. Finally, we will use repeated measures analysis for group (neurofeedback and placebo) x time (T0, T1, and six months follow-up, T2) to investigate the changes over time. To examine the possible effects of patient characteristics on the efficacy of the neurofeedback, the following variables will be assessed as covariates in the MANOVA and repeated measures analyses: age at assessment, age at diagnosis, diagnosis, time since diagnosis, and treatment modalities. All analyses will be conducted using SPSS. A *P*-value <0.05 will be considered significant.

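### Randomization is stratified by treatment module but the named analysis models omit module, which gives up some power if module predicts outcome beyond T0 and does not threaten validity

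*Protocol article*

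**What the plan says.** All references are to the protocol article.

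- **Neurofeedback treatment modules.** The baseline qEEG assigns each patient to one of three modules. Each has a placebo counterpart: "Three identical placebo treatment modules were matched to the three neurofeedback treatment modules". The indicated module is therefore known before allocation and defined identically in both arms.
- **Randomization.** "For stratfication purposes, randomization takes place after selection of the most appropriate neurofeedback treatment module". Allocation is made "using a randomization table generated by SPSS". Neither blocks nor separate lists per module are described.
- **Statistical analyses.** For the main comparison, "we will conduct multivariate analysis of variance (MANOVA) to determine the effect of neurofeedback post-treatment (T1) on the primary and secondary outcomes", and "T0 data will be included in the model as covariate". Change over time is examined by "repeated measures analysis for group (neurofeedback and placebo) x time (T0, T1, and six months follow-up, T2". The further covariates, introduced as patient characteristics, are "age at assessment, age at diagnosis, diagnosis, time since diagnosis, and treatment modalities".
- **Power calculation.** The sample size of 35 per arm is "Given an effect size of 0.6 with alpha set at 0.05 (one-sided) and a power of 0.80".

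The last covariate listed, on treatment modalities, stands beside diagnosis and time since diagnosis. It reads most naturally as tumor treatment. The article calls the neurofeedback types modules throughout.

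**The concern.** Module is the one factor by which the trial says it randomizes, yet no named model contains it. Module encodes the baseline beta 1 and SMR profile and decides which training an active patient receives, so it could plausibly relate to outcome. The T0 covariate is a test score, not an EEG profile, and need not capture that information.

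When allocation is balanced within strata, the between-stratum part of the outcome variance drops out of the treatment contrast. A model without the stratum term still counts that variance as residual error. It then reports a standard error larger than the real sampling variability, and the test rejects too rarely. At stake is some power in a trial of 70 patients whose Discussion section already anticipates losses during treatment and follow-up.

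**Working it through.** **Inputs from the article:** d=0.6, one-sided alpha 0.05, power 0.80, 35 per arm, three modules.

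**Assumptions, because the article gives no figure:**
- R2, the share of outcome variance explained by module after T0 adjustment, is taken from 0 to 0.20.
- The module split is taken as 44/16/10. The Discussion says only that these groups are small.
- One outcome is considered at a time, as in the plan's own power calculation.

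**1. The plan's figure.** n = 2(1.645 + 0.842)² / 0.6² = 34.3, rounded up to 35 per arm. This reproduces the stated number. The noncentral t gives power of 0.800 at 35 per arm one-sided, and 0.697 two-sided.

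**2. Standard error with balance within module.** Take the total SD as 1.
- Reported without module: √(4/70) = 0.239.
- Actual, and reported with module: √((1−R2)·4/70). At R2=0.10 this is 0.227.
- Ratio 1/√(1−R2): 1.026 at R2=0.05, 1.054 at 0.10 and 1.118 at 0.20. The reported standard error is too large by 2.6%, 5.4% and 11.8%.

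**3. Power with module.** Use the noncentral t with 66 df and noncentrality (0.6/√(1−R2))·√(35/2).
- R2=0: 2.510, one-sided power 0.799.
- R2=0.05: 2.575, power 0.817.
- R2=0.10: 2.646, power 0.835.
- R2=0.20: 2.806, power 0.871.

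**4. Like-for-like comparison.** The model without module has to be assessed under the same R2 and the same balance, because stratified allocation has already made its estimate more precise. Simulated trials with exact balance within the 44/16/10 split give:

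| R2 | One-sided power, without vs with module | Two-sided power, without vs with module | Two-sided type I error without module |
|---|---|---|---|
| 0 | 80% vs 80% | 70% vs 70% | about 5% |
| 0.05 | 80–81% vs 81–82% | 70% vs 72% | 4.3–4.6% |
| 0.10 | 81% vs 83% | 70% vs 74% | 3.9% |
| 0.20 | 82% vs 87% | 71% vs 79% | 2.8% |

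With module in the model, type I error stays at about 5% throughout. As a check on the last column, multiply the two-sided critical value 1.995 (68 df) by the ratio in step 2. This gives 2.047, 2.103 and 2.231, which correspond to about 4.5%, 3.9% and 2.9%.

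**5. If balance within module is not enforced.** Shuffling allocation over all 70 patients gives two-sided type I error without module of about 5% at R2=0.10 and 0.20, so the test is valid. One-sided power is still lower without module: 80% against 82% at R2=0.10, and 80% against 86% at R2=0.20.

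**The case against.** The strongest objection is scope. This is a journal article, the SAP is not shown, and handling of stratification factors is often settled there. The five covariates are listed to explore which patient characteristics affect efficacy, so module's absence from that list is silence and not a declared exclusion. That is fair, and the SAP may already contain the term. The point stands because the article does name its two models and the covariate it adjusts for, and the stratification factor is not among them.

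The second objection is size. No document gives an R2, and what counts is variance explained beyond T0. At R2=0.05 the one-sided loss is only 1 to 2 points, and at R2=0 there is none. This stands in full.

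Three stronger readings are tempting, and the article does not support them:

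- **That the benefit of stratifying is lost.** Balance between arms, unbiasedness and the actual precision of the estimate are all kept. Only the reported standard error and the test fail to reflect them.
- **That power would rise from 69.7% to 74.1% or 79.0%.** The starting figure is two-sided, whereas the plan's calculation is one-sided. It also belongs to a case in which module explains nothing. Compared under the same R2, the two-sided loss is about 4 points at R2=0.10 and 8 at R2=0.20.
- **That the test is certainly conservative.** This needs balance enforced within module. The Randomization section implies such balance but describes no blocks or separate lists.

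**Conclusion.** The point holds as an efficiency improvement that costs almost nothing. It is not a threat to validity: bias and inflated false-positive error do not arise under either allocation scheme. With balance within module, leaving module out costs about 2 points of power at R2=0.10 and 5 at R2=0.20 on the plan's one-sided basis, and next to nothing at R2 of 0.05 or less. These sizes rest on assumed values of R2 and an assumed module split. That the named models omit module rests on the article's text, including the reading of treatment modalities as tumor treatment. Whether the two-sided or the one-sided figures apply at analysis is a separate question and does not change this conclusion.

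**What to change.** Add the indicated module as a fixed factor with three levels to the T1 model and the repeated measures model. Code it by the qEEG indication, so that active and placebo patients with the same indication share a level. Do not use the six-level code that separates active from placebo, because it would absorb the treatment comparison. Do not test the treatment effect within modules, since the article itself notes how small those groups are. State the choice before unblinding, so that adjustment is not decided after the results are seen.

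The cost is 2 degrees of freedom. If module explains nothing, one-sided power stays at about 80% (0.7996 with 68 df, 0.7993 with 66 df). The indication is determined for every patient before allocation, so no new data and no change in procedure are needed.
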